**Inclusion criteria for the amputee group**
Aged between 18 and 65 yearsCompletion of prosthetic rehabilitation and having used a prosthesis for at least 1 yearHave a transradial level amputationUse of a 4-channel myoelectric-controlled transradial prosthesisResidual limb length between 5 and 25 cmA score of 3 or less on the visual analog scale for phantom or residual limb painA score of 15 or less on the Beck Depression InventoryA score of 26 or greater on the Standardized Mini-Mental State ExaminationNo diagnosis of any neurological, orthopedic, psychological (eg, schizophrenia and psychosis), or systemic diseaseVoluntary participation in the study
**Inclusion criteria for the control group**
Aged between 18 and 65 yearsNo diagnosis of any neurological, orthopedic, psychological, or systemic diseaseA score of 15 or less on the Beck Depression Inventory and 26 or greater on the Standardized Mini-Mental State ExaminationVoluntary participation in the study

Both groups will be included based on these criteria. No randomization will be applied between groups.

### Ethical Considerations

This study was approved by the noninterventional clinical research ethics committee of Istanbul Medipol University (E-10840098-202.3.02-2988) on May 9, 2024. All procedures will be conducted in accordance with the principles outlined in the Declaration of Helsinki. Before participation, all individuals will be informed about the study through both written and verbal explanations. Those who agree to take part will be asked to sign an informed consent form. The form explicitly states that participation is entirely voluntary and free of charge and that participants may withdraw from the study at any time without providing a reason or facing any consequences.

No additional costs will be incurred by the participants, and no compensation will be provided. All personal and identifying data will be kept strictly confidential. The collected data will be used solely for scientific purposes and without any commercial intent. Where necessary, anonymized data may be subjected to statistical analysis without the need for further ethics approval, provided that such use is covered by the initial consent.

### Study Design

This study is registered in the ClinicalTrials.gov database (NCT06541379) and uses a cross-sectional design with multicenter recruitment and single-center assessment. Participants will be recruited from several prosthetics and orthotics clinics located in Istanbul, Turkey, while all evaluations will be conducted at the prosthetics and orthotics research and application center of Istanbul Medipol University. All necessary institutional approvals were obtained before study initiation.

A total of 30 participants will be included: 15 (50%) individuals with unilateral transradial amputation who use a myoelectric prosthesis and 15 (50%) healthy control participants matched for age and sex. The study flowchart describing the recruitment and assessment process is presented in Figure 1.

**Figure 1 figure1:**
[figure not shown]
Study flowchart.

The study timeline and procedures are summarized as follows: ethics approval was obtained from the institutional ethics committee on May 9, 2024, and funding was received from the Scientific and Technological Research Council of Turkey (TÜBİTAK) on April 25, 2025. Participant recruitment and data collection started on April 25, 2025, with 15 participants planned per group. Assessments and interventions include tests of MI ability, upper limb functional tests, and proprioception test. Follow-up will include ongoing monitoring and assessment of all participants. Data analysis will be completed after all data are collected. The study is expected to be completed in June 2026.

The sampling frame consists of all eligible individuals with unilateral transradial amputation who meet the inclusion criteria across the collaborating clinics during the recruitment period. Participants will be recruited consecutively, applying identical inclusion and exclusion criteria across centers.

Although participants will be recruited from different clinics, all assessments will be performed by a single trained researcher (the first author) using the same equipment and standardized procedures at the prosthetics and orthotics research and application center. This approach ensures measurement consistency and minimizes the risk of selection bias.

This study was reported in accordance with the STROBE (Strengthening the Reporting of Observational Studies in Epidemiology) statement for cross-sectional studies (Multimedia Appendix 1). The related TÜBİTAK 1002-A project report is provided in Multimedia Appendix 2.

### Outcome Measures

According to the study hypothesis, the primary outcome is MIA assessed using the MIQ-3, which was selected as the primary end point given its central role in prosthetic motor control, motor learning, and functional adaptation in individuals who have undergone transradial amputation.

The secondary outcomes include the following:

Upper-limb functional performance, assessed using the Box and Block Test (BBT), Jebsen-Taylor Hand Function Test (JTHFT), and the Disabilities of the Arm, Shoulder, and Hand (QuickDASH) questionnaireMI performance indicators, including the Mental Chronometry Test (MCT) and hand mental rotation task, as secondary measures of MIAProprioceptive and sensorimotor accuracy, measured by joint position sense (JPS) error using a validated digital goniometer app (DrGoniometer [CDM SrL])General balance and flexibility, evaluated by the Functional Reach Test (FRT) as an indicator of overall functional stabilityCognitive and psychological screening, including the Standardized Mini-Mental State Examination (SMMSE), Beck Depression Inventory (BDI), and Visual Analog Scale (VAS) for pain intensity

Each participant will be assessed once, as this is a cross-sectional study with no intervention. To minimize potential bias, all assessments will be performed by trained evaluators following standardized protocols. Participants will be recruited according to predefined eligibility criteria to reduce selection bias, and data will be systematically recorded to prevent information bias. As no intervention is applied, performance bias is not applicable.

To minimize the risk of type I error resulting from multiple comparisons, the Bonferroni correction will be applied to secondary outcome analyses.

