## Methods

### Participants

The required sample size for the study was determined using G*Power software (version 3.1; Heinrich Heine University Düsseldorf). The calculation was based on the Movement Imagery Questionnaire-3 (MIQ-3) scores reported by Saimpont et al [27], which served as a reference for the primary outcome of this study.

Although Saimpont et al [27] reported a large effect size (Cohen *d*=1.41) in a healthy population, a more conservative estimate (Cohen *d*=0.8) was applied in this study’s power analysis to better reflect expected variability among participants who underwent transradial amputation. Using a 2-tailed independent samples *t* test, with an α of .05 and power (1–β) of .80, the required total sample size was calculated as 30 participants (n=15, 50% per group).

This sample size provides sufficient statistical power to detect large effects (Cohen *d*≥0.8) between groups while also allowing for potential participant dropouts. A sensitivity analysis showed that detecting moderate effects (Cohen *d*=0.6) would require approximately 18 participants to achieve equivalent power; however, as the study primarily aims to detect large between-group differences, the planned sample of 30 participants (n=15, 50% per group) was considered adequate.

Participants will be recruited from prosthetics and orthotics centers located in Istanbul, Turkey. The study group will consist of volunteers who meet the inclusion criteria; therefore, no probabilistic sampling method will be used. Inclusion criteria for the amputee and control groups are listed in Textbox 1.

Inclusion criteria for the amputee and control groups.

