**Missing data, outliers, and multiple comparisons**
Missing data will undergo listwise deletion.Trials with outlier values exceeding 2 SDs from the group mean will be excluded. Sensitivity analyses with and without outliers will be performed.The Bonferroni correction will be applied for multiple comparisons.

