**Significance**
All tests will be 2-tailed, with *P*<.05 considered statistically significant.

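### The Bonferroni correction is valid, but Holm's step-down procedure gives the same familywise error control, never rejects less, and gains up to about 7 points of power per test

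*Protocol article*

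**What the plan says.** Under Outcome Measures, after listing the secondary outcomes, the protocol article gives limiting type I error as the purpose and says that "the Bonferroni correction will be applied to secondary outcome analyses". In the Statistical Analysis textbox, the entry on missing data, outliers and multiple comparisons says "The Bonferroni correction will be applied for multiple comparisons", without restricting this to secondary outcomes. The Significance entry adds "All tests will be 2-tailed, with *P*<.05 considered statistically significant".

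Neither statement names a step-down variant. Bonferroni without qualification ordinarily means the single-step rule, in which each P value is compared with .05 divided by the number of tests in the family, m. The article does not give m. That can be left to a fuller document and is not the point here.

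The design inputs stand under Participants. The calculation is described as "Using a 2-tailed independent samples *t* test", "with an α of .05 and power (1–β) of .80", and "a more conservative estimate (Cohen *d*=0.8) was applied in this study’s power analysis". It arrives at 15 participants per group.

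**The concern.** The multiplicity method is named outright, so it is a stated choice and can be judged as one. The aim is to limit type I error across several tests. Another procedure meets that aim to the same level, needs no further assumption, and can only add rejections. With 15 per group the secondary tests are short of power before any correction, so a method that gives some of it away without better error control deserves a second look. What is at stake is the number of real secondary effects that the study declares. Its validity is not in question.

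**Working it through.** **Inputs from the article.** 15 per group; two-sided tests at .05; planning effect d=0.8. The article also cites a reference study that "reported a large effect size (Cohen *d*=1.41) in a healthy population".

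**Assumptions.** The family size is taken as m=4, 7 or 20. Seven corresponds to one test each for the Box and Block Test, Jebsen-Taylor, QuickDASH, mental chronometry, hand rotation, joint position sense and functional reach. Twenty stands for counting subtests, angles and sides separately. Four is a small illustrative family. Correlation between tests is 0.4. Two-sample t tests stand in for the planned analyses.

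**Step 1: the article's own figure.** With d=0.8, two-sided .05, power .80 and independent groups, the t test needs 25.5, so 26 per group and 52 in total. At 15 per group the power is 56%. The stated 30 does not reproduce. That is a separate matter, but it sets the baseline: an uncorrected test has 56% power.

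**Step 2: single-step Bonferroni at 15 per group, d=0.8 (exact t).**

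- m=4: .05/4 = .0125, power 33%
- m=7: .05/7 = .00714, power 26%
- m=20: .05/20 = .0025, power 16%

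**Step 3: why Holm has the same error control.** Order the P values. Compare the j-th smallest with .05/(m−j+1) and stop at the first failure. Suppose m0 nulls are true. The first true null to be rejected has rank at most m−m0+1, so its threshold is at most .05/m0. A false rejection therefore requires some true-null P value to be at or below .05/m0. By the Bonferroni inequality that has probability at most m0 × .05/m0 = .05, whatever the dependence. Every Holm threshold is at least .05/m, so nothing that Bonferroni rejects is lost.

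**Step 4: size of the gain.** Simulation, 15 v 15, d=0.8 on each real effect, correlation 0.4, 15,000 to 40,000 runs per scenario. Figures are average power per real effect; repeat runs differ by about one point.

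| Tests | Real | Bonferroni | Holm |
|---|---|---|---|
| 4 | 4 | 33% | 40% |
| 4 | 2 | 33.5% | 35.2% |
| 4 | 1 | 33% | 33% |
| 7 | 7 | 26% | 33% |
| 7 | 3 | 26% | 27% |
| 20 | 20 | 16% | 19% |
| 20 | 10 | 16% | 17% |

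In every scenario the chance of at least one rejection was identical for the two methods (for example 68% for both with four tests all real). No run had a Bonferroni rejection that Holm missed. With all effects real, Holm added at least one rejection in about 22% of simulated studies for m=4 and about 27% for m=7.

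**Step 5: sensitivity to the effect.** At d=1.41, m=7 and all effects real, power goes from 82% to 92–94% (correlation 0.5 and 0). With 3 of 7 real it goes from 82% to 84–85%.

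**The case against.** The strongest reply is that nothing here is wrong. Bonferroni controls type I error under any dependence, the article never claims that it is the most powerful method, and no other section contradicts it. That stands, and it is why this is an optional improvement.

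A reader might infer that Holm has strictly more power at no cost. The article and the arithmetic do not support that:

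- Holm gains only after a first rejection at .05/m, so the chance of finding anything at all is unchanged.
- The 7-point gain needs every effect to be real. The Discussion cites earlier work in which prosthesis users performed much like healthy people on hand mental rotation, so some secondary nulls may well be true. With about half real, the gain is 1 to 2 points.
- Bonferroni has simple simultaneous confidence intervals that match its tests, and Holm does not. This counts for little here, because the Statistical Analysis section plans no adjusted intervals and judges significance by P values.

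A reader might also take the correction to cover only a handful of amputee-versus-control comparisons. The wording is wider: correlations, regressions and dominant-side comparisons are planned as well, and the textbox statement is not confined to secondary outcomes. Holm's advantage holds for any family, but the remedy must not narrow that scope.

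Finally, 16 participants have already been assessed, and the article says assessor blinding was not feasible. A move to a less conservative rule should therefore be documented openly. The Results section says that no statistical analysis has yet been run, so it can still be prespecified.

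**Conclusion.** The point holds as an efficiency suggestion. For hypothesis testing at familywise .05, Holm is at least as powerful as Bonferroni in every case and more powerful when several effects are real. At the planning effect d=0.8 with 15 per group, the gain is about 0 to 7 percentage points per real effect: the top of that range when all of four or seven effects are real, 1 to 2 points when about half are, and essentially none when only one is. These sizes rest on the assumed family sizes, a correlation of 0.4, equal effects and t tests in place of the planned covariance analyses. The ordering of the two methods rests on none of these.

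The low power of the secondary tests does not come mainly from this choice. An uncorrected test has only 56% power at d=0.8, and Holm does not change that.

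**What to change.** In Outcome Measures and in the textbox entry on multiple comparisons, replace the Bonferroni correction with the Holm step-down (Holm-Bonferroni) procedure at familywise .05. Keep the families and the scope of each statement as they are; in particular, do not limit the textbox entry to secondary outcomes, which could remove cover from the MIQ-3 subscale comparisons. Report Holm-adjusted P values. Record the change as a dated, justified amendment before any analysis.

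The cost is one phrase in two places, a short amendment, and ordering the P values. No new data are needed. Holm uses the same family size as Bonferroni, so that definition is needed under either method. What is given up is the simple set of simultaneous confidence intervals that matches Bonferroni, which the plan does not call for. If the investigators want such intervals, keeping Bonferroni is defensible.

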### Demographic Information

Demographic data will be collected through face-to-face interviews using a standardized data collection form developed by the research team. The recorded variables will include age, sex, height, weight, BMI, educational level, occupation, year and cause of amputation, dominant side, side of amputation, duration of prosthesis use, current medication use, and history of previously used prosthetic systems. For individuals with transradial amputation, stump length will be measured using a tape measure as the distance from the olecranon to the most distal end of the residual limb.

### SMMSE Description

The SMMSE is a brief 30-item test designed to assess cognitive functions, including attention, memory, orientation, calculation, language, and visuospatial skills. In this study, it will be used solely for participant eligibility screening. Individuals scoring 26 or higher will be included [28].

### BDI Description

The BDI is a 21-item self-report questionnaire used to measure an individual’s level of depression. Each item is rated on a scale from 0 to 3. In this study, only individuals with a score of 15 or lower will be included [29].

### VAS Description

The VAS is a measurement tool rated from 0 to 10 used to assess pain intensity. In this study, individuals who have undergone amputation with a VAS score of no more than 3 for phantom or residual limb pain will be included [30].

### MIQ-3 Description

The MIQ-3, originally developed by Williams et al [31], will be used to assess imagery ability in all individuals included in the amputee and control groups. The Turkish validity and reliability study of this questionnaire was conducted by Dilek et al [32]. The MIQ-3 consists of 12 items and evaluates internal visual imagery, external visual imagery, and kinesthetic imagery abilities through 4 actions for each domain. These actions include leg raising, jumping, shoulder flexion, and forward bending. The movements are designed to assess MI capacity in internal, external, and kinesthetic dimensions.

Participants will initially perform each movement physically. They will then be asked to mentally perform the same movements as a cognitive task. This mental imagery task will be rated using a 7-point Likert-type scale (1=very hard to see or feel and 7=very easy to see or feel). For scoring, the average score of the 4 movements corresponding to each subdimension will be calculated.

### MCT Description

MCT is an objective method used to evaluate the temporal accuracy of MI [33]. In this study, the MCT will be administered using the BBT. Participants will first be asked to physically transfer 15 blocks from one compartment to another, and the time taken will be recorded. Subsequently, the same task will be mentally imagined after removing the test apparatus from view. The duration for the imagined transfer of each block will be verbally indicated by the participant and recorded accordingly.

The difference between the actual and imagined durations will be used to calculate the mental chronometry ratio, using the following formula:

mental chronometry ratio = |actual time − mental time| / actual time

A ratio closer to 0 indicates that the imagined movement duration closely approximates the actual movement, reflecting a higher level of MIA.

### Orientate Mobile App Description

The Orientate app (Reflex Pain Management Ltd) is a rehabilitation tool focused on MI and laterality recognition (left and right discrimination). It is used to assess mental rotation ability. Participants will be presented with 25 hand images at various angles and asked to determine, as quickly as possible, whether each image depicts a left or right hand. The number of correct and incorrect responses, the number of skipped trials, and reaction times will be recorded [34].

### BBT Description

The BBT is a widely used standardized assessment tool for evaluating gross motor skills and hand function. Originally developed by Mathiowetz et al [35], the test uses 150 wooden cubes, each measuring 2.5 cm, and a wooden box divided into 2 compartments. Participants are instructed to transfer as many cubes as possible, 1 at a time, from one compartment to the other within 60 seconds while seated at a table. The total number of cubes successfully transferred will be recorded as the test score (Figure 2).

**Figure 2 figure2:**
[figure not shown]
Box and Blocks Test in a participant who has undergone transradial amputation. The participant moves blocks between compartments within 60 seconds using the prosthetic hand.

### JTHFT Description

The JTHFT, originally developed by Jebsen et al [36], will be used as a performance-based assessment to evaluate hand function in activities of daily living. The test will include various types of grasps and will assess the speed at which participants complete specific tasks. Standardized materials, which will be readily available in clinical settings, will be used for the test. Participants will be required to complete 7 distinct tasks: writing, turning over cards, picking up small objects, simulated feeding, stacking checkers, picking up large light objects, and picking up large heavy objects. Each task will be performed separately with both the dominant and nondominant hands. The test score will be calculated based on the time taken by participants to complete each task (Figure 3).

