### JPS Description

To evaluate proprioceptive function relevant to prosthetic control, the JPS assessment will be used. JPS measures an individual’s ability to replicate a given joint angle and can be conducted using combinations of passive and active movements, under eyes-closed conditions [22].

Considering the amputation levels of the individuals who have undergone transradial amputation, all participants will undergo JPS assessment of the shoulder and elbow joints, performed bilaterally (dominant and nondominant sides where applicable) with standardized positioning while standing comfortably with feet shoulder-width apart and arms relaxed at the side before each trial. In the amputee group, assessments will be conducted with the prosthesis worn and the terminal device maintained in the closed position to ensure consistency across participants. For passive JPS, the investigator will move the limb to the target angle (eg, 30°) and then return it to the starting position, and the participant will estimate the joint angle without moving it. Participants’ vision will be occluded during assessment to prevent visual feedback, ensuring blinding to the target angle. For active JPS, the investigator first demonstrates the target angle with the participant’s eyes open. Subsequently, with eyes closed, participants actively replicate the joint angle without any physical guidance.

For the shoulder joint, angles of 90° abduction and 90° flexion will be used; and for the elbow joint, angles of 30°, 60°, and 90° flexion will be assessed. All joints will be positioned consistently at the same starting reference point for each trial to ensure measurement consistency across participants. Each angle will be measured 3 times, and the mean value will be recorded. Trials with outlier values exceeding 2 SDs from the mean or trials with measurement errors will be excluded.

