**Motor imagery (MI) variables**
Measures will include the Movement Imagery Questionnaire-3, including its subscales: kinesthetic MI, internal MI, external MI, and total score as well as the Orientate app accuracy and completion time, and motor execution time–MI time for the dominant and nondominant hand.Comparisons will be performed using the analysis of covariance, adjusting for age, dominance, and residual limb length.If the analysis of covariance assumptions are not met, nonparametric alternatives will be applied.

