**Amputee-specific analyses**
Dominant-side amputation will be coded as a binary variable (yes or no).Differences in MI, functional outcomes, and proprioception outcomes between participants with amputation of the dominant limb and participants with amputation of the nondominant limb will be analyzed using appropriate parametric or nonparametric tests.Associations with MI outcomes will be examined using correlation and regression analyses.

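### MCT, JTHFT and JPS are labelled by dominant and nondominant side, which in unilateral amputees puts prosthetic-side and intact-side data under one label (secondary outcomes only)

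*Protocol article*

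**What the plan says.** The Study Design section describes the amputee group as "individuals with unilateral transradial amputation who use a myoelectric prosthesis". Each amputee therefore has one prosthetic and one intact side.

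Three measures carry dominance labels:

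- **Jebsen-Taylor Hand Function Test (JTHFT Description):** "Each task will be performed separately with both the dominant and nondominant hands".
- **Joint position sense (JPS Description):** "performed bilaterally (dominant and nondominant sides where applicable". The section adds "In the amputee group, assessments will be conducted with the prosthesis worn", but does not name the amputated side as the one analysed.
- **Mental Chronometry Test (Textbox 2, Motor imagery (MI) variables):** the variable compared between groups is "motor execution time–MI time for the dominant and nondominant hand".

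The two association blocks of Textbox 2 (MI and upper limb function, MI and proprioception) list JTHFT subtests and joint angles without a side. Their regressions adjust for age, dominance and residual limb length, and dominance is not defined. The JPS Description also names tested side as a covariate, but Textbox 2 does not repeat it.

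The amputee-specific block expects both kinds of amputation, since it compares "participants with amputation of the dominant limb and participants with amputation of the nondominant limb". It states "Dominant-side amputation will be coded as a binary variable (yes or no" and also plans correlation and regression with the imagery outcomes. The Demographic Information section records "dominant side, side of amputation, duration of prosthesis use".

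**The concern.** If some amputees lost the dominant limb and others the nondominant limb, a dominant-hand variable is prosthesis performance in the first set and intact-limb performance in the second. The nondominant-hand variable is the reverse. Neither describes prosthetic-side function.

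The study wants to know how imagery relates to function and proprioception in myoelectric prosthesis users. For these three measures, a variable that mixes the two sides gives group differences and associations that are hard to interpret and probably too small. With 15 amputees there is little information to spare.

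**Working it through.** The protocol gives no figure on this point. Its only calculation is the sample size for MIQ-3, and nothing here depends on it.

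**Step 1. Does mixing occur?** It is avoided only if all 15 amputees lost the same side relative to dominance. With p the share of dominant-side amputations, and independent participants, that probability is p^15 + (1−p)^15. This is 0.00006 at p = 0.5, and 0.0047 at p = 0.3 or 0.7. The amputee-specific block itself presupposes both kinds.

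**Step 2. Group difference.** Scale scores so that the intact hand has mean 0 and SD 1, and assume that controls perform like the intact hand. Let the prosthetic hand differ by D. The expected group difference is p·D on the dominant hand and (1−p)·D on the nondominant hand. At p = 0.3 and D = 2 these are 0.6 and 1.4. At p = 0.5 and D = 4 both are 2.0.

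**Step 3. Correlation with imagery among amputees.** Let the prosthetic-hand SD be s, its correlation with imagery ρ, and the intact-hand correlation 0, with imagery distributed alike in the two subgroups.

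- Unadjusted: r = p·ρ·s / √(p·s² + (1−p) + p(1−p)·D²)
- Adjusted for dominant-side amputation: r = p·ρ·s / √(p·s² + (1−p))

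The adjustment removes the mean shift, the term p(1−p)·D². The numerator still averages a prosthetic-hand slope with an intact-hand slope.

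The inputs are assumptions, none of them in the documents: ρ = 0.6, D from 2 to 4, s from 1 to 2, p from 0.3 to 0.7. Two worked cases:

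- p = 0.5, D = 4, s = 1: unadjusted 0.30/√5 = 0.13; adjusted 0.30/√1 = 0.30.
- p = 0.7, D = 2, s = 2: unadjusted 0.84/√3.94 = 0.42; adjusted 0.84/√3.1 = 0.48.

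| p | r, dominant hand, unadjusted | r, adjusted for dominant-side amputation |
|---|---|---|
| 0.3 | 0.09–0.22 | 0.18–0.26 |
| 0.5 | 0.13–0.32 | 0.30–0.38 |
| 0.7 | 0.20–0.42 | 0.42–0.48 |

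Coded as prosthetic side, the correlation stays at 0.60 and the group difference at D.

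**Step 4. Sensitivity to the intact-hand assumption.** A zero intact-hand correlation works in the concern's favour. If it were also 0.6, with s = 1 and p = 0.5, the numerator would be 0.5·0.6 + 0.5·0.6 = 0.6. The adjusted value would then be 0.60, with no dilution. The unadjusted value would be 0.6/√2 = 0.42 at D = 2 and 0.6/√5 = 0.27 at D = 4. The unadjusted correlations suffer either way. The adjusted ones suffer only to the extent that the two slopes differ.

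**The case against.** **Only one measure is explicit.** For JTHFT and JPS, the text describes testing both sides, which is sensible in unilateral amputees. The association analyses name no side, and which side enters a model is often left to a fuller plan. This stands in part: only for mental chronometry is dominance fixed as the analysis variable, and the JTHFT photograph caption shows the prosthetic hand. But dominance is the only side label given for analysing these three measures, and Textbox 2 is presented as the detailed plan. Carrying the given labels forward produces the mixture.

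**There are safeguards.** Tested side is to be adjusted for, dominance is a covariate, and the amputee-specific block plans correlations and regressions as well as a subgroup comparison. These help, as the adjusted column shows. As additive terms they do not separate two slopes, the plain correlations carry no adjustment, and the amputee-specific block does not say which side is the outcome.

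**Stronger readings that the documents do not support.**

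- A reader might infer that the function and group results in general fail to describe prosthesis function. MIQ-3, the primary outcome, and QuickDASH are not side-specific. The Box and Block Test is not organised by dominance, and its caption states that the prosthetic hand is used.
- A reader might infer a near-total loss of correlation by assuming a very large gap between hands in blocks moved. That applies the mixture to the Box and Block Test, where the protocol does not show it, and leaves out the planned adjustment. JPS is measured at the shoulder and elbow, joints retained after transradial amputation, so a large gap cannot be carried over to it.
- A reader might infer that a two-peaked variable invalidates the planned tests. The plan checks normality and provides nonparametric alternatives. Ranking does not unmix the sides, but that is a different matter.

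**Conclusion.** The point holds for the secondary side-specific outcomes: explicitly for mental chronometry, and for JTHFT and JPS if their testing labels become analysis labels. Group differences would shrink to roughly the share of amputees whose prosthesis is on the labelled side. A prosthetic-hand correlation of 0.6 would appear as about 0.1 to 0.4 unadjusted and 0.2 to 0.5 adjusted.

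Those figures are illustrations. They rest on the assumed hand gap, SD ratio, subgroup split and zero intact-hand correlation, and the loss is smaller where the sides differ less, as may be so for JPS. The direction does not depend on the exact values, provided that the sides differ in mean or in slope.

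No prosthesis data are lost, because amputation side and dominant side are both recorded. Severity is moderate: an analysis variable is badly defined, and the primary comparison is untouched.

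**What to change.** In the three association and comparison blocks of Textbox 2:

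1. Define the mental chronometry, JTHFT and JPS variables in amputees as prosthetic (amputated) side and intact side. Make the prosthetic side the main analysis variable and the intact side secondary.
2. Give each control a comparison side whose dominant or nondominant status mirrors that of the matched amputee. The protocol says only that controls are matched for age and sex. If matching is not individual, assign sides to reproduce the amputee group's distribution.
3. Define the dominance covariate as whether the analysed side is the participant's dominant one, and reconcile it with the tested-side covariate in the JPS Description.
4. Keep dominant-side amputation as the descriptor in the amputee-specific block.

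The cost is a change of wording and recoding of recorded data, with no new measurement. The Results section reports that no statistical analysis had been run as of November 2025, so this can still be fixed before any results are seen. Left until afterwards, the choice of side would be open to the data.
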